#### Data collection methods

This project applies several data collection formats, including data collection on paper, directly into netbooks and by accelerometer. All paper-collected data is entered into spreadsheets and double-checked for data entry quality through pre-defined steps. We use netbooks (Gateway® LT2000) to collect survey data. All the surveys are designed into the LimeSurvey™ (Version 1.91) on netbooks. Data from netbooks is backed up on regular basis and eventually stored in a central server. Data collected by accelerometer are uploaded to the *polargofit.*com web service and a report of each child’s activity per 24-hour period is produced in Microsoft Excel format.

### Intervention

The NSFS project consists of four major component interventions in the areas of nutrition, physical activity, economic and art-community engagement to induce behavioral change in our target population in order to achieve obesity prevention (Table 3). Each component is explained in detail below.

**Table 3 T3:** Description of intervention components

**Behavior area**	**Focus**	**Intervention**	**Target**	**Frequency**	**Intensity**
Nutrition	Family nights	Educational workshop focusing on nutrition and health messages	Any adult member of each eligible family	Monthly	One hour
	School curriculum	Nutrition education by UCCE in elementary school and preschool	Eligible child		
Physical Activity	School curriculum	SPARK physical activity program in elementary school and preschool	Eligible child	4 days/week	20 minutes
Economic	Voucher	Each family with one eligible child receives a $25 voucher/month that can be used towards the purchase of fruits and vegetables	Family of eligible child	Monthly	$25/month/family
Art community engagement	Community events	Art projects in community or messaging healthy behaviors	Community	NA	NA

#### Nutrition

The nutrition intervention consists of two components a) family nights and b) a school-based program. Family nights are led by a local health educator and are based on a series of focus groups to understand community perceptions of childhood obesity including barriers, opportunities, interpretation and prioritization of key prevention messages recommended by the American Academy of Pediatrics [34]. The nutrition team consists of University of California, Cooperative Extension (UCCE) nutrition staff, advisors and specialists; UCD faculty and graduate students; and local staff based in Firebaugh. Based on focus group data and findings from other studies, the team develops a three-year plan for family nights, including key messages, recommendations on logistical issues (space, length of classes), and a plan for evaluation. In this study, cultural adaptation begins with nutrition curricula and approaches that work well in the general low-income audience served by UCCE. The local health educator who lives in the community is trained in basic nutrition, safe food handling, adult education and learner-centered delivery techniques and meets with the nutrition specialist each month to modify messages and activities. Adapted lessons are piloted with one group of participants to incorporate group feedback before delivering the lesson to the rest of the families. Each lesson is approximately one hour in duration and includes facilitated discussion, a hands-on activity (such as label reading or meal planning), and a food demonstration and tasting of a recipe containing fruits and/or vegetables. Families are required to attend at least five of the ten classes offered each year (15 minimum over three years) to remain in the program. Any adult member of each eligible family can participate in the family nights to receive credit for attendance.

In coordination with UCCE Fresno County, school-based nutrition education is delivered to children in the classroom. Staff from the UCCE, CalFresh and Expanded Food and Nutrition Education Program (EFNEP) are involved in program support. Age-appropriate UCCE curricula include “Happy Healthy Me”, “Reading Across MyPyramid” and “Farm to Fork”. A UC CalFresh program representative provides the lesson plans, foods for tasting activities and other materials to the classroom teachers, along with training on how to deliver the lessons. The classroom teacher determines the actual number of lessons taught each year. Routine program evaluation provides records of teacher perception of student improvement in nutrition skills and behaviors and the number of lesson delivered.

#### Physical activity

The physical education curriculum used for students in the intervention arm is based on the Sport Play and Active Recreation for Kids (SPARK) curriculum. Materials include the Early Childhood (ages 3–5) curriculum binder and the K-2 curriculum binder [35]. Each curricular component is presented in scope and sequence via daily lesson plans that are aligned to the National Association for Sport and Physical Education (NASPE) Standards. The SPARK K-2 curriculum also contains academic integration tips (with a special emphasis on literacy), social skills themes by grade level, and challenging extensions for each activity [36]. The SPARK curriculum was chosen for the school physical activity intervention based on its successful use in several studies [37].

In grades K-2, implementation of the physical activity curriculum is carried out by a local teacher trained in SPARK and employed by the intervention school district. During the intervention, the SPARK trained teacher works with 19 K-2^nd^ grade teachers and approximately 300 children each week, delivering 20–30 minute exercise sessions to each class. All 19 K-2 grade teachers receive SPARK curriculum binders and CDs and share the use of SPARK equipment, housed in a central storage area on the school campus. In addition to the physical activity sessions delivered by the teacher, all K-2^nd^ grade teachers integrate SPARK activities into their class lessons so that the children receive an average of 66 minutes of physical education each week.

For intervention site preschools, a program research staff member trained in SPARK Early Childhood assists the preschool teachers in integrating the curriculum into their lesson plans. Twelve teachers from eight pre-schools sites receive Early Childhood SPARK curriculum and equipment and dedicate an average of 71 minutes each week to the activities.

#### Economic

The economic intervention consists of providing participating families in Firebaugh with monthly fruit and vegetable vouchers worth $25/month. Participating families receive the monthly payments throughout the three-year intervention period. This approach provides incentives to families to purchase more nutritious and healthier foods. Vouchers are allocated per family regardless of the number of eligible children, family size or composition. A “family” for voucher purposes is described as an eligible child and a guardian, and the members directly related to them who consume food using the same resources. The list of fruits and vegetables that families can purchase using their vouchers matches the list of fruits and vegetables used by the WIC program. Unused voucher money expires at the end of the month and the card is automatically reloaded. Vouchers can only be used at the Firebaugh Supermarket and market staff are responsible for ensuring that funds are spent on approved purchases. Families must attend nutrition classes or check-in with the NSFS staff on a monthly basis to continue receiving funds. If a family does not check-in during a given month, their card is frozen until they regain contact with program staff. This ensures that the cards are still within the participant’s possession and have not been lost or stolen. Additionally, NSFS staff collect food purchase receipts from participants on a monthly basis and transfer these receipts to the UCD team for processing.

#### Community art

Community art tools and strategies, including murals, are used to engage and involve community members. A summer mural project in the comparison community of San Joaquin is carried out through collaboration between UCD faculty, staff, undergraduate students, as well as members of the community including local high school students. The UCD team recruits local community members to participate in mural development activities, including mural content meetings. Once the content is finalized, the team spends approximately two weeks in the community painting the mural. Through this community-based project, members of the UCD team engage local high school students in discussions about their community’s culture and history and about their educational aspirations.

A corresponding series of community-based art interventions also occur within the intervention community of Firebaugh. These interventions include a series of limited edition screenprints that provide a visual representation of the proposed interventions.

### Statistical analysis

#### Sample size calculation

During the baseline phase of the study, all eligible children and their families in both Firebaugh and San Joaquin are approached. Based on an initial estimation of the total number of children from previous years, we anticipated that our sample would contain approximately 400 children in each group. This number of subjects is sufficient to detect an effect difference between groups in the mean change in standardized BMI (z-scores) of as small as 0.20 standard deviations with 80% power. In a previous study with Latino school children, a change of that magnitude was achieved over a two-year period.

Our sample constructs a multi-cluster formation of students, classrooms, grades, schools and cities. Because we are not assigning multiple cities to each group, we have to assume that the matching of cities will take care of any clustering problem at the city level. However, accounting for clustering is a problem in sample size calculation because there is really no way of estimating in advance the within-cluster correlation (r) with respect to any of the outcome variables. To our knowledge this information is not available from other studies. If we assume that r = 0.01 among school grades in schools and there are an average of 143 students per grade then based on the design effect formula (DE = 1 + (n-1)*r), the detectable effect difference in primary outcome will be 1.56 * 0.20 standard deviation with 80% power in this study. Based on the school’s estimation there will be less than a 5% mobilization rate within the targeted schools. All new students who fall in our sampled cohort will be eligible for the study.

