**Discussion:**

We present a study methodology for an obesity prevention intervention in communities with unique environmental conditions due to rural and isolated location, limited infrastructure capacity and limited resources. This combined with numerous cultural considerations and an unstable population with limited exposure to researcher expectations necessitates reassessment and adaptation of recruitment strategies, intervention delivery and data collection methods. Trial registration # NCT01900613.

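### The 80% power stated for 0.20 SD holds only if children are independent; under the plan's own design effect it is about 44%

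*Protocol article*

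**What the plan says.** All of this is in the protocol article, under Sample size calculation.

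- All eligible children in both towns are approached, and "we anticipated that our sample would contain approximately 400 children in each group".
- The article calls that number sufficient for this target: "an effect difference between groups in the mean change in standardized BMI (z-scores) of as small as 0.20 standard deviations with 80% power". The sentence does not say that clustering is ignored.
- The support for 0.20 SD is one earlier result: "In a previous study with Latino school children, a change of that magnitude was achieved over a two-year period".
- The next paragraph turns to clustering: "Our sample constructs a multi-cluster formation of students, classrooms, grades, schools and cities". It says the within-cluster correlation cannot be estimated in advance. It then takes a single value ("If we assume that r = 0.01 among school grades in schools") with an average of 143 students per grade, and gives the usual design-effect formula.
- It concludes that "the detectable effect difference in primary outcome will be 1.56 * 0.20 standard deviation with 80% power in this study".
- With one city per arm, city-level clustering is assumed to be removed by matching.

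The section gives no alpha, no sidedness and no number of grade clusters per arm.

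**The concern.** Two statements about the same 400 children per group stand side by side, each with 80% power: one for 0.20 SD and one for 1.56 times that. The sample is clustered by the plan's own account, so only the second can describe this study. The first is the one that is called sufficient and tied to earlier evidence. When the detectable difference rose by more than half, neither the sample size nor the target effect was revisited, and nothing was offered to show that 0.31 SD is attainable.

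What is at stake is how a null result would be read. Someone relying on the first statement would take it as good evidence against an effect of the cited size. Under the plan's own assumptions, such a result would be more likely than not even if the true effect were 0.20 SD.

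**Working it through.** **Inputs.** From the sample size section: 400 per group, difference 0.20 SD, power 80%, r = 0.01, cluster size m = 143, DE = 1 + (m − 1)r. Assumed: two-sided alpha 0.05. This reproduces the plan's 400; one-sided 0.05 would give 88% power and does not. All effects are in SD units of the change in BMI z-score.

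**1. The plan's unadjusted figure.**
- n per group = 2(1.96 + 0.842)² / 0.20² = 393.
- With 400: SE = √(2/400) = 0.0707, and power = Φ(0.20/0.0707 − 1.96) = 80.7%.

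The figure reproduces, for independent children.

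**2. The plan's adjusted figure.**
- DE = 1 + 142 × 0.01 = 2.42, and √DE = 1.556, so the multiplier 1.56 is correct.
- 1.56 × 0.20 = 0.312 SD. Directly: (1.96 + 0.842) × √(2 × 2.42/400) = 0.308 SD.

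This also reproduces.

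**3. Power at 0.20 SD under the same inputs.**
- Effective n = 400/2.42 = 165 per group.
- SE = √(2 × 2.42/400) = 0.110.
- Power = Φ(0.20/0.110 − 1.96) = Φ(−0.142) = 44.4%. One-sided 0.05 gives 57%.
- For 80% power at 0.20 SD: 393 × 2.42 = about 951 per group.

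**4. Range over r** (m = 143, 400 per group, normal approximation).

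| r | DE | Power at 0.20 SD | Difference detectable with 80% power |
|---|---|---|---|
| 0 | 1.00 | 81% | 0.20 SD |
| 0.005 | 1.71 | 58% | 0.26 SD |
| 0.01 | 2.42 | 44% | 0.31 SD |
| 0.02 | 3.84 | 30% | 0.39 SD |
| 0.05 | 8.10 | 17% | 0.56 SD |

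**5. Number of clusters.** The 0.31 SD uses normal quantiles. The article does not give the number of grade clusters; 400/143 = 2.8 implies about three per arm. The table assumes k clusters per arm, a test with 2(k − 1) degrees of freedom, noncentral t, r = 0.01 and two-sided 0.05.

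| Clusters per arm | df | Power at 0.20 SD | Power at 0.312 SD | Difference detectable with 80% power |
|---|---|---|---|---|
| 3 (400 per arm with DE 2.42; 3 × 133; or 3 × 143 = 429) | 4 | 29–30% | 57–60% | 0.40–0.41 SD |
| 4 (400 per arm with DE 2.42, or 4 × 100) | 6 | 33–39% | 66–74% | 0.34–0.37 SD |
| 5 × 80 | 8 | 46% | 82% | 0.30 SD |

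The result at 0.31 SD therefore depends on the cluster count. The shortfall at 0.20 SD does not: power there is below 80% in every row.

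**The case against.** The strongest defence is that the plan hides nothing. It gives 0.20 SD first, raises clustering next, and states the adjusted difference itself, with the right multiplier. A reader might infer that the section contradicts itself or contains a calculation error. The documents do not support that: both figures reproduce, and they read as before and after an adjustment. What remains is that the first sentence carries no such label and is the only one backed by evidence.

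A reader might also infer that 0.31 SD is simply not detectable with 80% power. That rests on a cluster count inferred from 400/143 and on a test that the article does not specify and may leave to an analysis plan. The 143 could be the school roll and not the enrolled children. Table 1 also admits nearly five birth years, so five clusters of 80 are conceivable, and those would keep about 82% power. The few-cluster result is conditional.

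The earlier effect was reached over two years, whereas the primary hypothesis here concerns three years. So 0.31 SD is not shown to be out of reach; the article only gives no support for it.

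Three further arguments are tempting but not needed:

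- **Attrition.** The abstract speaks of "an unstable population with limited exposure to researcher expectations", but the sample size section cites mobility below 5% and admits new students. A single 5% loss (380 per group) moves power at 0.20 SD only from 81% to 79% without clustering, and from 44% to 43% with it. Larger losses would have to be assumed.
- **Cluster size.** The physical activity section says one teacher works with "approximately 300 children each week" in K-2 of the intervention district, or about 100 per grade. The 143 is an average over grades and districts that are not stated, so the two may describe different populations.
- **Siblings.** A family-level design effect needs a family size and a correlation that the article does not give.

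**Conclusion.** The point holds as a misstated power claim. At 0.20 SD, the only effect the plan supports with evidence, 400 per group gives about 44% power under the plan's own r = 0.01 and 143 per grade, not 80%. This assumes a two-sided 5% test; one-sided 5% gives 57%. For r between 0.005 and 0.05 the figure runs from 58% down to 17%.

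The study's detectable difference at r = 0.01 is the 0.31 SD that the plan reports. That figure makes no allowance for few clusters. With about three grades per arm and between-cluster degrees of freedom, it would have about 57–60% power, and the difference detectable with 80% power would be about 0.41 SD. With five clusters of 80 it would hold.

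Every figure here is conditional on matching having removed city-level variation, which one city per arm cannot test.

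**What to change.** In the sample size section:

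1. Label 0.20 SD as the difference detectable without clustering, and stop calling the sample sufficient for it.
2. Present 0.31 SD as the study's detectable difference at r = 0.01, with about 44% power at 0.20 SD. State the alpha and sidedness used.
3. Add the range over r, with power at 0.20 SD of 58% at 0.005, 30% at 0.02 and 17% at 0.05.
4. State the number of grade clusters per arm and whether 143 counts enrolled children or the school roll. Note that with about three clusters a test on between-cluster degrees of freedom has about 57–60% power at 0.31 SD and detects about 0.41 SD with 80% power, while five clusters of 80 keep about 82% at 0.31 SD.
5. Say that all of these figures depend on matching having removed city-level variation.

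The cost is a few sentences and a less favourable stated power. All eligible children are already approached, so the correction does not call for more.

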## Discussion

Careful consideration and strategies are required to maximize recruitment and retention of this hard to reach population of both the intervention and comparison communities. An important consideration is that farm work employment peaks during the months of April to October when many family members work long hours in the field. Strict adherence to using *promotores*, local staff, and/or field researchers to contact participants is required to contact participants to conduct informed consent, surveys and medical measurement. Further, relying on standard appointments for participants does not guarantee they show up at appointment time. It is therefore often required that program staff make visits to the families’ homes to conduct recruitment and/or data collection procedures. In addition, program staff works with the school nurse to schedule anthropometric measurements of children during the school day.

Recruitment and retention of participants for the comparison community of San Joaquin also presents a unique set of challenges. For example, the comparison site lacks office space that would provide visibility to the project in that community. Because of funding limitations, project staff use space available from local organizations such as churches and the community center. This may compromise the stability of staff access to the community at large in the comparison community. Also, since there is no active nutrition intervention in San Joaquin, project staff anticipated more problems with recruitment and retention. Therefore, focus groups were used to develop a series of workshops that focus on family well-being and ways in which parents can support their children’s education. These will be offered monthly to all community members. Workshop attendees invite other community members who are eligible to participate in the study. This strategy increases the community members’ interest in NSFS and the enrollment of participants.

In the implementation of the nutrition education component, careful selection of adequate space is critical to establish an environment where adults can relax and learn. However, a main challenge is securing a suitable site in the community for family night, i.e., a safe, quiet, adequate space for childcare, and a convenient location. For example, a potential site (a closed school site) seemed to meet all criteria but was later found to harbor asbestos. Securing access to a second site, a classroom in the local community college, required more than six months of negotiation between UCD and the college to formalize liability management.

Another critical factor for success of nutrition education is cultural adaptation and tailoring of nutrition messages. Interventions delivering culturally-adapted, family-centered nutrition education to Latino families with preschool children have reported improvements in BMI status of the children [4,5]. To make the content culturally relevant and engage participants in this study, the local educator must use open-ended, problem-solving questions in small group discussions (10–12 parents). Food demonstrations of recipes, a monthly raffle, and free childcare were other aspects of the Family Nights that served as a cultural draw.

A number of administrative issues occurred during the initial implementation of the fruit and vegetable vouchers. The voucher payments are distributed via automatically reloading US Bank debit-style cards. During the initial month of distribution, US Bank switched the reload date from the first of the month to the 25^th^ of the month without previous notification. Furthermore, there is a delay in processing transactions between the retails store and US Bank. For these reasons, card use has been restricted between the 20^th^ and 28^th^ of each month. Participants chose to have restrictions on use rather than receiving a larger allotment of funds at one time because it would be too cumbersome to track larger balances. The balance on each card is not reported at the time of use and balance check information through US Bank is only available in English. Due to these factors, Spanish-speaking participants must individually keep track of remaining funds or call the field office for assistance.

The retail environment provides another set of challenges toward implementation. Retail storeowners and employees are required to be trained on voucher use and protocol. The economic voucher may be used with other forms of payment and employees are not used to these types of complicated transactions. Furthermore, participants are not able to combine the WIC fruit and vegetable voucher with the economic voucher during the first four months of intervention. Store employees process WIC payments in a way that does not allow them to be combined with other forms of payment. A large number of our participants also participate in WIC and are therefore inconvenienced by this issue.

Collection of scanner data also imposes complications. The retail store in the comparison community severed our relationship just prior to implementation. They were not going to receive a financial incentive to allow scanner data collection and decided it was not in their interest to participate. Scanner data collection has been ongoing in the intervention community but needs to be translated by a computer programmer for analysis. Furthermore, scanner systems are extremely technical and need to be constantly monitored by specialize staff.

The implementation of the physical activity intervention was helped significantly by the decision of superintendent to support physical activity at the intervention site by hiring a local teacher to teach SPARK physical activity to K-2^nd^ graders each week. However, a challenge for the physical activity intervention occurred when the team realized that lead teachers attending one SPARK training were not allowed by the SPARK Program to return to the schools to train other teachers. SPARK requires that 50% of the teachers attend the SPARK training or SPARK trainers come to the district to train the teachers. Unfortunately, both options required funding levels beyond the budget. However, it was learned that the SPARK curriculum is available for direct purchase for teachers to use in their classrooms without formal training, as the binders are very clear and easy to follow. The research team decided to buy the SPARK curriculum and equipment for the teachers and although the teachers received no formal training, the K-2^nd^ grade teachers were able to watch the local SPARK trained teacher instruct the lessons and they could then duplicate this lessons in their classrooms. The physical activities at the pre-school levels were very basic and pre-school teachers easily integrated the activities into their daily activities with minimal coaching from the research team.

In sum, the unique environmental condition of the study that is rural and isolated locations with limited infrastructure capacity, the distance of the university research team from the local community, combined with limited resources and unstable population with limited exposure to researcher expectations necessitated adaptation reassessment of recruitment strategies and data collection methods by the research team.

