Due to participants living in isolated communities with limited exposure to outsiders and the mixed immigration status of community members, developing trust between the research team and community members is important to allow for effective family recruitment and participation. A locally visible site location within the intervention community with Spanish-speaking staff is critical to project implementation. In addition, Spanish-speaking university researchers and students assist with participant recruitment. Several recruitment approaches are utilized including: (1) door-to-door recruitment (2) meet and greet events, (3) one-on-one/personal networks, (4) school events (back to school nights, child pick up drop off intervals), (5) Parent Teacher Meetings, (6) open market or *remate* informational booths, (7) community events (e.g., Day of the Dead, Red Ribbon Week), (8) religious organizations, and 9) community health fairs. In order to improve participation, food and raffles are offered. A master information sheet of all recruited families is used to track eligible, ineligible, refusal and dropout families. In order to track the completion of required activities for each family, an activity-tracking log records the progress. Each family must complete baseline surveys and anthropometric measures in order to join the program intervention activities in both sites.

Upon approval by UCD’s Institutional Review Board (IRB) of all data collection procedures and instruments, informed consent is obtained from legal guardians of eligible children, including fathers, mothers and/or grandparents. Informed consent is obtained through two primary methods: (1) face to face verbal review of all documents at the study field office or at participants’ homes, or (2) group presentations at the field office in the intervention site or at community events in the comparison site. A presentation is used for both individuals and groups in order to accommodate low literacy among participants and to facilitate better understanding of the research and assist in the consent process.

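### BMI follow-up depends partly on programme engagement that differs by town, so loss of the primary outcome may differ by town and bias the comparison

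*Protocol article*

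**What the plan says.** The primary outcome is the rate of BMI growth. It is compared between the towns after three years of intervention and measured every six months in both (Study instruments). Table 2 lists school, health fair, project office and home as the measurement settings.

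Contact with families is organised differently in the two towns:

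- **Expected retention.** The Discussion says of the comparison town: "Also, since there is no active nutrition intervention in San Joaquin, project staff anticipated more problems with recruitment and retention". It adds that this town has no project office and that staff use borrowed space.
- **Office.** Subject eligibility and recruitment says: "A locally visible site location within the intervention community with Spanish-speaking staff is critical to project implementation".
- **Voucher.** Only Firebaugh families receive $25 a month, for three years. Under Economic: "If a family does not check-in during a given month, their card is frozen until they regain contact with program staff".
- **Removal.** Subject eligibility and recruitment excludes families that do not complete all surveys and measurements. Nutrition requires five of ten family-night classes a year to stay in the programme; family nights are part of the intervention.
- **Routes initiated by staff.** The Discussion says home visits are often needed, and that "program staff works with the school nurse to schedule anthropometric measurements of children during the school day".

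**The concern.** The towns are compared on children who still have BMI measurements at later waves. If the chance of being measured depends on engagement, and engagement is supported differently in each town, the measured children may no longer be comparable even if the enrolled children were. Firebaugh families have a financial reason to stay in touch and an office to visit; San Joaquin families have neither. The removal rules add a further link between engagement and staying in the data, and one of them belongs to an intervention component. What is at stake is bias in the primary comparison. That is a separate matter from the power lost when fewer children are measured, and a larger sample would not cure it.

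**Working it through.** **1. The plan's own figure.** Sample size calculation expects "approximately 400 children in each group" and a detectable difference "as small as 0.20 standard deviations with 80% power". Alpha is not stated; I assume 0.05, two-sided. Then n = 2 × (1.960 + 0.842)² / 0.20² = 393 per group, and 400 per group gives power 0.807. The figure reproduces, but only if all 400 per group are analysed. The section's one loss figure, school mobility below 5%, is not split by town.

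**2. The stated clustering.** DE = 1 + (143 − 1) × 0.01 = 2.42 and √2.42 = 1.56. This matches the statement that "the detectable effect difference in primary outcome will be 1.56 * 0.20 standard deviation with 80% power", which is 0.312 SD.

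**3. Bias from unequal loss.** Let L be the proportion lost in a town. Let g be the mean BMI z-score change of lost children minus that of retained children, in SD units, the same in both towns. The full mean is the retained mean + L × g, so the retained mean is the full mean − L × g. For Firebaugh minus San Joaquin, the observed difference is therefore the true difference + (L_SJ − L_FB) × g.

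**4. Assumed inputs.** The document gives no retention by town and no value for g. I take 10% and 30% lost, a 20-point difference, and g of size 0.2 to 0.5:

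- 0.20 × 0.2 = 0.04 SD
- 0.20 × 0.3 = 0.06 SD
- 0.20 × 0.5 = 0.10 SD

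This is 20% to 50% of 0.20 SD, or 13% to 32% of 0.312 SD. The shift is zero if g = 0. It changes sign if Firebaugh loses more, or if lost children gain less BMI than retained ones.

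**5. Effect on the error rate with no true difference.** Average loss of 20% leaves 320 per group. The standard error is √(2/320) = 0.0791 under independence, and 0.0791 × 1.556 = 0.1230 with DE 2.42. The rejection probability is P(Z > 1.96 − b/SE) + P(Z < −1.96 − b/SE), where b is the bias:

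| Bias b (SD) | Independence | DE 2.42 |
|---|---|---|
| 0.04 | 0.080 | 0.062 |
| 0.06 | 0.118 | 0.078 |
| 0.10 | 0.244 | 0.13 |

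**6. Power, for comparison.** With 10% and 30% lost (360 and 280 analysed), power at 0.20 SD falls from 0.807 to 0.709 under independence.

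**The case against.** The strongest reply is that BMI follow-up does not hang on rewarded contact. School is a listed setting, and home visits and school-nurse sessions are initiated by staff and tied to neither voucher nor classes. A frozen card is reactivated once contact resumes. San Joaquin has promotores, an advisory council and monthly workshops, at which food receipts are collected. The article may also leave the choice of default setting to a fuller document.

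Much of this stands, and it rules out two stronger readings that a reader might infer. One is that BMI data will certainly be lost differently by town: the text reports an anticipated problem and a response to it, not attrition rates. The other is that San Joaquin must lose more of its poorly engaged families: the five-of-ten class rule could remove just such families in Firebaugh, and the text does not say whether removed families are still measured.

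It does not remove the point. The workshops' described effect is interest in the study and enrolment, not six-monthly measurement. Nothing in the text makes school the route for every child at every wave. The rule on incomplete surveys could also exclude a child who was measured at school. The point concerns data collection and exclusion as the article describes them, not a missing-data method that an analysis plan would supply.

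**Conclusion.** The point holds as a risk that the protocol itself partly foresees. Follow-up of the primary outcome depends in part on engagement that is supported and enforced differently in the two towns, so loss may differ by town and bias the comparison of BMI growth. Direction and size cannot be determined from the document.

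The illustration (a shift of 0.04 to 0.10 SD either way; error of about 8% to 24% under independence, about 6% to 13% with the design effect of 2.42) rests wholly on an assumed 20-point difference in loss, an assumed gap of 0.2 to 0.5 SD that is equal in both towns, and an assumed two-sided 5% test. The design-effect range is the fairer guide to error, because it uses the protocol's own clustering assumption. The shift in SD is the same in either case. This is a worthwhile and cheap improvement to the design, not a demonstrated failure of it.

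**What to change.** - Make the school-day session arranged with the school nurse the default BMI measurement at every wave, in both districts. It should cover every enrolled child attending a district school or preschool, whatever the family's class attendance, check-in, voucher or survey status.
- State that these measurements stay in the primary analysis even if the family has stopped programme activities or surveys, subject to continued consent. Reword the exclusion for incomplete surveys or measurements to match; otherwise school measurement alone need not preserve the data.
- Use home visits and the other settings for children not reached at school.
- Report completed BMI measurements by town and wave.

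The cost is protocol wording, some school time and scheduling with the nurses. The document gives no nurse or staff capacity, so the workload should be checked with both districts. Families are recruited with children aged 2 to 5, so early waves will include children not yet in school; they, and children who leave the district, still need the other routes. Recruitment was still under way when the article was submitted, so at that stage later waves could still be changed.
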